#### Happiness

Happiness is determined using the Subjective Happiness Scale (SHS), which provides a subjective assessment of an individual’s overall happiness or unhappiness (Lyubomirsky and Lepper, 1999). The SHS consist of four items and seven response options ranging from 1 to 7. Scores between 4 and 28 are possible, with higher scores indicating higher levels of happiness. The SHS was adapted and validated for use in the Brazilian population in a study with 600 Brazilian adults, and it showed a satisfactory reliability index, with an alpha of 0.82 (Damásio et al., 2014).

## Data collection and management

Data will be collected online via the OneUS app. A sociodemographic questionnaire and measures of well-being, optimism, hope, happiness, and stress will be used. Data will be stored in an online database. Data collected online will be automatically stored on a local server (CentOS Linux Dedicated on Google Cloud Platform). In accordance with the LGPD (Brazilian General Data Protection Law), it is necessary to ensure the rights to freedom and privacy when processing personal data of participants, regardless of whether it is in digital or physical environments. To ensure accuracy and minimize errors, a researcher will periodically review and verify the input and accuracy of the data that is being entered. To improve adherence to the intervention, participants will receive notifications and motivational messages *via* app and email. In addition, the app has a feature that will inform users of their participation level and remind them to continue their training when the weekly participation rate is below the desired level.

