The rapid advance of digital innovation has led to the availability of more than 350,000 health apps in major mobile app stores around the world. Among them, 47% are dedicated to well-being, according to data from IQVIA Institute for Human Data Science (2021). Despite the abundance of options, most apps lack adequate evaluations to determine their effectiveness in promoting and improving well-being (Donker et al., 2013). Although a recent meta-analysis suggests that health apps offer promising benefits in improving well-being, the overall effect size remains small based on pooled analysis (g = 0.17, 95% CI 0.05 to 0.29, *p* = 0.004) (Eisenstadt et al., 2021), and there is limited information on the long-term sustainability of these benefits beyond the intervention period (Boiler and Abello, 2014). Mobile apps are valuable tools that can provide quick and accessible benefits to many people; however, it is crucial that these apps are evidence-based to ensure their effectiveness and mitigate any potential adverse effects caused by their use.

Thus, a smartphone app named OneUS has been developed to support people in cultivating well-being through positive thinking and positive emotions (gratitude, hope, pride, love, and serenity). The app utilizes intentional mental training techniques and includes a library of psychoeducational content and guided exercises. By increasing awareness and teaching skills to cultivate positive emotions and train positive thinking in daily lives (Bekhet and Zauszniewski, 2013; Fredrickson, 2013), OneUs aims to enhance overall well-being. The app offers content in various formats, such as videos, audio, and text, which are enabled weekly after the completion of the visualization and activities. The app sends notifications and reminder messages to motivate users to continue the training, which will increase adherence rates.

This study aims to evaluate the effectiveness of a mobile app-based positive psychology intervention to improve people’s well-being through the daily practice of activities aimed at positive emotions and positive thinking. The study will test the hypothesis that using the OneUS mobile application for the daily practice of positive emotions and positive thinking enhances well-being and reduces psychological distress in a sample of adults from the general Brazilian population.

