## Participants

### Sample size

This study will be conducted in Brazil. Participants will be recruited through advertising messages on social networks. In these messages, potential participants will find a link to a Google form to make an initial registration and provide their email addresses. The study aims to include 200 eligible participants, 100 per condition (active control and experimental). The General Linear Mixed Model Power and Sample Size 3.0 calculator (GLIMMPSE 3.0) (Kreidler et al., 2013) was used to determine the required sample size considering the study design, fixed predictors of conditions (active control and experimental), Time (t1, t2, t3, t4, t5, t6, t7, and t8), and Conditions x Time interaction effects. Using Hotelling Lawley Trace with power 0.8 and type I rate 0.05, total sample size was calculated as 76; however, 100 participants per condition will be selected to account for potential dropouts.

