### Active control condition

The comparator will be an active control condition. Participants in this condition will be trained in mental imagery exercises in normal everyday life situations. This condition will be considered an active control because the participants will perform mental imagery of neutral events and emotion monitoring. The app design for this condition will have the same structure as the experimental condition and will include a user profile, menu, assessment measures, and notifications.

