## Outcome measures

The outcome measures will be completed at 8 time points: baseline (t1), intervention (t2, t3, t4, t5, t6) post-intervention (t7), and 3-month follow-up (t8), following the recommended timeline outlined in the SPIRIT 2013 statement (refer to Table 2). The SPIRIT 2013 statement serves as a checklist for clinical trial protocols, offering guidelines on the essential content and a standardized diagram of activities, interventions, and measures (Chan et al., 2013).

**Table 2 tab2:** Schematic diagram for timeline participant.

	Enrolment	Baseline	Intervention					Close-out	Follow-up
TIMEPOINT	*0*	*t1*	Week 1 (t2)	Week 2 (t3)	Week 3 (t4)	Week 4 (t5)	Week 5 (t6)	*t_7_*	*t8*
Enrolment:									
Eligibility screen	X								
Informed consent	X								
Allocation	X								
Interventions:									
Training and daily practice of positive emotions and positive thinking									
Active control									
Assessments:									
Socio-demographic characteristics	X								
Well-being		X	X	X	X	X	X	X	X
Optimism		X	X	X	X	X	X	X	X
Hope		X	X	X	X	X	X	X	X
Subjective Happiness		X	X	X	X	X	X	X	X
Stress		X	X	X	X	X	X	X	X

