The main strength of the present study lies in the development of an evidence-based mobile health application aimed at promoting well-being. The use of a randomized controlled trial design minimizes bias and provides a rigorous means of assessing the impact of the intervention. The intervention is based on intentional mental training, a psychological mechanism that has been shown to be highly effective in improving well-being (Dahl et al., 2020). Through coaching, feedback exercises and daily practices, this mobile-based intervention could have a direct implication on daily lives of the participants by increasing their positive emotions and positive thinking, potentially improving their overall well-being. On the other hand, the present study has the following limitations: healthy participants from the general population will be included, so the results obtained cannot be generalized to clinical populations. Another limitation is the lack of an effective adherence strategy to ensure the completion of the training by the participants. However, in order to increase the adherence rate to the program, notifications and reminder messages will be sent by the app and *via* email to motivate the participant to continue with the training. Also, the number of participants was expanded to overcome the dropout rate during the intervention.

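### Outcomes are collected through the app with no off-app route stated, so people who stop using it are likely to be missing at t7 and t8; an e-mailed link at those two visits would cheaply reduce the reliance on missing at random

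*Protocol article*

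**What the plan says.** The Data collection and management section of the protocol article names the route: "Data will be collected online via the OneUS app". The next sentence shows that this covers the primary and all secondary outcomes: "A sociodemographic questionnaire and measures of well-being, optimism, hope, happiness, and stress will be used". The control condition works the same way, since its app "will include a user profile, menu, assessment measures, and notifications" (Active control condition). Outcome measures and Table 2 schedule every scale at all eight time points, ending with post-intervention (t7) and the 3-month follow-up (t8). The training itself lasts five weeks.

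E-mail addresses are collected at pre-registration (Sample size). After enrolment, the stated use of e-mail is adherence: "To improve adherence to the intervention, participants will receive notifications and motivational messages", through the app and by e-mail.

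On drop-out, the Sample size section gives a calculated total of 76 and then says that "100 participants per condition will be selected to account for potential dropouts". The Discussion lists as a limitation the "lack of an effective adherence strategy to ensure the completion of the training by the participants", and points to the reminders and the expanded sample as the response.

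Data analysis methods plans a linear mixed model with condition, time and their interaction, fitted by maximum likelihood.

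**The concern.** When the product under test is also the measuring instrument, leaving the product tends to end measurement. Someone who loses interest in week 2 and removes the app will probably not answer in the app at t7, and less probably still at t8, months after the programme has ended. The people whose outcomes are hardest to predict from earlier visits are then the people without late data.

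Enrolling more people does not cure this. It keeps the standard error acceptable, but the extra participants go missing for the same reasons. Reminders may reduce the loss, but they do not give a view of those who leave anyway.

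At stake are the t7 and t8 contrasts on well-being, which carry the claim of effectiveness and durability. The missing-at-random assumption would bear much of the weight there, and in-app data alone could not test it.

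**Working it through.** **1. What the sample size allows.** Inputs from Sample size: 76 calculated, 200 planned. Implied allowance: 1 − 76/200 = 0.62. For comparison, 76/(1 − 0.20) = 95 and 76/(1 − 0.40) = 127. The article states no drop-out rate, so 62% is the most loss the plan could absorb and still hold 76, not a forecast. The 76 itself cannot be reproduced, because the article gives no mean pattern, SD or correlation. This point does not depend on it.

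**2. What the model estimates.** Let D be the effect at t7 in those who continue, d the proportion who stop and have no later data, and k the fraction of benefit that stoppers keep. Suppose for simplicity that stopping is unrelated to outcome.

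- Effect in all randomised: D × [1 − d × (1 − k)]
- Maximum-likelihood estimate: about D, since unseen visits are projected from those who stayed
- Overstatement: D × d × (1 − k)

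D, d and k are assumptions. With D = 0.30 SD:

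| Loss d | ML estimate | All randomised, k = 0 | All randomised, k = 0.5 | All randomised, k = 1 |
|---|---|---|---|---|
| 20% | 0.30 | 0.24 | 0.27 | 0.30 |
| 40% | 0.30 | 0.18 | 0.24 | 0.30 |
| 62% | 0.30 | 0.11 | 0.21 | 0.30 |

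Simulated trials with the planned fixed effects, 200 participants and an assumed within-person correlation of 0.6 agree with the k = 0 column: the mean estimate is 0.30 at each loss rate.

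**3. Independent check at t8.** A second simulation used an assumed 0.5 SD effect, correlation 0.6 and an unstructured covariance. With the effect lost on stopping, the all-randomised effect was 0.40, 0.30 and 0.20 SD at 20%, 40% and 62% stopping, while maximum likelihood returned 0.50 to 0.52. With the effect kept, both were about 0.5.

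When stopping depended on the last observed score (38% in the app arm, 20% in control), the methods separated:

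| After stopping | All randomised | Completers only | ML mixed model |
|---|---|---|---|
| Effect lost | 0.31 | 0.62 | 0.51 |
| Effect kept | 0.50 | 0.62 | 0.50 |

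So the planned model is not a completers' analysis. It corrects for loss that observed scores explain, but not for a change that follows stopping.

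**4. What off-app collection would do.** Suppose a proportion r of stoppers is recovered at t7 and benefit is wholly lost on stopping. The estimate is then roughly D(1 − d)/(1 − d + rd).

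- r = 0.5: 0.24/0.90 = 0.27; 0.18/0.80 = 0.225; 0.114/0.69 = 0.17
- r = 0.8: 0.24/0.96 = 0.25; 0.18/0.92 = 0.20; 0.114/0.876 = 0.13

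The targets are 0.24, 0.18 and 0.11. Partial recovery shrinks the gap without closing it. In simulation at 62% loss, the standard error of the t1-to-t7 contrast falls from about 0.18 to between 0.13 and 0.15. With complete data it would be √[2 × 2(1 − 0.6)/100] = 0.126.

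**The case against.** A reader might infer more than the text supports, in five ways.

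- **That the app is the sole route.** The article names a platform and does not exclude others. A fuller protocol could hold one.
- **That stopping training and leaving assessment are one event.** Nothing says that questionnaires lock when training lapses, and a person can skip exercises and still answer. The Introduction's remark on materials "which are enabled weekly after the completion of the visualization and activities" concerns training content, not scales, so it gives no support. By t7 and t8 the programme has ended for those on schedule.
- **That the analysis reports the effect in continuing users.** The model uses all observed visits and, under missing at random, targets the effect had everyone continued. The second table in the working shows the difference.
- **That the sponsor expects 62% loss, or that bias is certain.** The text speaks only of potential drop-outs, and the Discussion's concession is about completing the training. The bias figures follow from assuming that benefit ends on stopping. The Introduction's theory is of lasting personal resources, which points the other way. The Discussion, however, cites a review in which lasting benefit was more likely in those who kept participating, so the question is open.
- **That the stated aim is the effect in all randomised.** The article does not say so. Its hypothesis refers to use of the app for daily practice.

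Size also matters. At 20% loss even total loss of benefit gives a gap of 0.30 − 0.24 = 0.06 SD, about half the complete-data standard error of 0.126.

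All of this limits the claim. It leaves intact that one collection route is stated, that none is described for people who leave the app, and that reminders and a larger sample do not remove any bias from those still lost.

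**Conclusion.** The point holds as a conditional weakness and a cheap improvement. Outcomes in both arms are collected through the app and no off-app route is given, so those who stop using it are likely to lack t7 and t8 data. The mixed model then relies on missing at random at the two time points that matter most.

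The size depends on what happens after stopping, which the documents do not establish. With an assumed 0.30 SD effect, the overstatement relative to all randomised runs from nil (benefit persists) to 0.06, 0.12 and 0.19 SD (benefit wholly lost) at 20%, 40% and 62% loss. The effect size, correlation and loss rates are assumptions; only the 62% ceiling derives from the article's figures. Confidence is medium, since a fuller protocol may already provide for off-app collection.

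**What to change.** In Data collection and management, state that at t7 and t8 the PERMA-Profiler and the secondary scales are also sent by e-mailed web link to every randomised participant in both arms, on a fixed date counted from randomisation, whether or not the app is still used or modules are completed. Participants who stop training stay in assessment unless they withdraw consent. Record whether each form was completed in the app or by link.

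The recovered scores of stoppers would also give some direct evidence on the missing-at-random assumption, which supports a sensitivity analysis for data not missing at random.

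The cost is protocol wording and one web form. The trial already holds e-mail addresses, sends e-mail messages and uses an online form for registration. The downside is two modes of completion at t7 and t8, which is why the mode should be recorded. The change must be in place before participants reach t7, because missed assessments cannot be recovered later.

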## Data analysis methods

Statistical methods for primary and secondary outcomes.

The analysis will be conducted using linear mixed models. This statistical approach is well-suited for handling the structure of the repeated measures inherent in our experimental design, enabling us to model the fixed effects of conditions (OneUS app intervention and Control active) and time (t1, t2, t3, t4, t5, t6, t7, and t8) and Conditions x Time interaction effects (DeHart and Kanpla, 2019). We will conduct data analysis using Maximum Likelihood Estimate (MLE) to calculate model parameters. This method allows for simultaneous estimation of all model parameters, including the variance of random effects. To ensure the validity of the model, we will verify the normality of the residuals. Hypothesis tests will be conducted to assess the significance of the fixed effects. The analyses will be carried out using the R statistical language (R Core Team, 2023) in the RStudio environment, utilizing the most up-to-date versions of the lme4 packages at the time of analysis.

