## Procedures

### Randomization and blinding

Participants will be randomly assigned to either the intervention condition or the active control condition using R software (Version 4.0.5) and the R package randomizr. The allocation ratio will be 1:1. The randomizr function, applied by a blinded research assistant, will randomly assign a value of 0 or 1 to each participant, representing their experimental condition (0 = Experimental; 1 = Active Control). Although participants and evaluators will not be blinded to the intervention during the study, the data analysts will be blinded. Participants may be able to determine which condition they are in due to the educational and informative content they receive about positive emotions and positive thinking.

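### The planned lme4 mixed model is not tied to the unrestricted-covariance test that sized the trial; with a random intercept or slope and serially correlated scores, the 5% Condition x Time test would run at about 5% to 10%

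*Protocol article*

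**What the plan says.** The section on data analysis methods plans linear mixed models with fixed effects of condition, time (eight levels) and their interaction. The software is R, "utilizing the most up-to-date versions of the lme4 packages at the time of analysis". On estimation it says: "We will conduct data analysis using Maximum Likelihood Estimate (MLE) to calculate model parameters". It mentions the variance of random effects without saying which random effects are meant. Normality of the residuals is the only model check named. The form of the hypothesis tests and their degrees of freedom are not given.

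The outcome section sets the schedule: "baseline (t1), intervention (t2, t3, t4, t5, t6) post-intervention (t7), and 3-month follow-up (t8".

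The sample-size section uses a different framework: "Using Hotelling Lawley Trace with power 0.8 and type I rate 0.05, total sample size was calculated as 76". Enrolment is then raised: "however, 100 participants per condition will be selected to account for potential dropouts". Allocation is 1:1. No correlation between measurements is stated anywhere.

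**The concern.** lme4 has no residual-correlation term. Two scores from one person are correlated only through the random effects. A random intercept implies the same correlation for every pair of visits; adding a slope relaxes this in one direction only. Self-reports taken through a five-week programme and again three months later would be expected to agree more closely between neighbouring visits than between baseline and follow-up. Where the fitted covariance misses that pattern, the interaction test refers its statistic to the wrong distribution.

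The sizing test makes no such restriction, because the Hotelling-Lawley trace accepts any covariance among the eight measurements. So the 0.05 in the sample-size section belongs to a test that the analysis section does not commit to. Checking residuals for normality does not help, since serially correlated residuals can be perfectly normal.

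At stake is the error rate of the Condition x Time test, which carries the comparison of the arms over time.

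**Working it through.** **The plan's own figure.** N = 76 cannot be reproduced, because no effect size, standard deviation or correlation is given. What it implies can be stated. With two arms and eight occasions, the Hotelling-Lawley test of the interaction is an F test on 7 and N − 8 = 68 degrees of freedom. Power of 0.80 at 0.05 needs noncentrality 15.9, that is, a Mahalanobis distance between the arms' change profiles of √(4 × 15.88 / 76) = 0.91.

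**Inputs from the article.** 100 per arm; 8 occasions, so 7 interaction degrees of freedom; nominal level 0.05; ML; lme4.

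**Assumptions.** Complete data; a person effect with half the variance, plus AR(1) deviations with correlation ρ per week; t1 to t7 at weeks 0 to 6 and t8 at week 18. The half share fixes the adjacent-week correlation at 0.5 + 0.5ρ (0.75 at ρ = 0.5). It does not affect the random-intercept results, because within-person contrasts remove the person effect.

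**Random intercept.** Let C be a 7 × 8 orthonormal contrast matrix and λ₁…λ₇ the eigenvalues of CΣCᵀ. Under the null, with N = 200:

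- between-arm sum B = Σ λⱼ χ²(1), error sum E = Σ λⱼ χ²(N − 2);
- F = (B/7) / (E/[7(N − 2)]), referred to F(7, 1386), which is the REML-type test;
- LR = 7N ln(1 + B/E), referred to χ²(7), critical value 14.07, which is the ML likelihood-ratio test.

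Both references are right (the second approximately) only when all λⱼ are equal. From 200,000 draws per row, with ε = (Σλ)² / (7Σλ²) measuring the departure:

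| ρ | ε | F test | ML likelihood ratio |
|---|---|---|---|
| 0 | 1.00 | 4.9% | 5.1% |
| 0.3 | 0.91 | 5.7% | 5.9% |
| 0.5 | 0.77 | 6.8% | 7.0% |
| 0.7 | 0.63 | 8.2% | 8.4% |
| 0.9 | 0.44 | 10.3% | 10.5% |

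Treating the eight visits as equally spaced changes little: 7.3% at ρ = 0.5 and 10.5% at ρ = 0.9 for the likelihood ratio. With 38 per arm (N = 76), the likelihood-ratio test runs from 5.6% at ρ = 0 to 10.9% at ρ = 0.9.

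**Random intercept plus slope.** Fitted by ML to 2,000 simulated trials per cell, 100 per arm, Wald χ². Ranges cover both spacings: 5.2% at ρ = 0, 5.7–6.1% at 0.3, 6.7–7.7% at 0.5, 8.3–8.5% at 0.7, 8.1–9.8% at 0.9. The slope does not remove the inflation.

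**How much is due to ML.** With a correctly specified random intercept, the ML likelihood-ratio test rejects when F(7, 7(N − 2)) exceeds (e^{14.07/(7N)} − 1)(N − 2). At N = 200 the threshold is 2.000, giving 5.2%; at N = 76 it is 1.983, giving 5.6%.

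With an unstructured covariance, the same test rejects when F(7, N − 8) exceeds (e^{14.07/N} − 1)(N − 8)/7. At N = 200 the threshold is 1.999, giving 5.7%; at N = 76 it is 1.975, giving 7.1%. The exact F reference gives 5.0% in both. So freeing the covariance while keeping ML and a χ² reference would not fully restore 5%.

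**The case against.** The strongest reply is that this is a condensed article. It names no random-effects structure, no form of test and no degrees-of-freedom method, and such details usually sit in a fuller document. No sentence states a wrong covariance, and the sample-size and analysis sections do not contradict each other: both name condition, time and their interaction. This stands in part. It makes the inflation conditional on what is fitted. It does not remove the point, because the article does commit to a package without residual correlation and to a check that cannot detect the problem.

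A second reply is that lme4 can mimic an unstructured covariance with one random effect per occasion. That needs 8 × 9 / 2 = 36 covariance parameters plus the residual variance, 37 in all, for a matrix with 36 distinct entries. With one score per occasion the residual variance is not identified, and the planned residual check loses its meaning. It is not an ordinary fit, and if intended it should be stated.

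Three stronger readings are tempting and are not supported:

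- A reader might infer that the test will run at 6% to 10%. That needs a serial correlation and a random-effects form that the article does not give; with little serial correlation the size is close to 5%.
- A reader might blame the maximum-likelihood sentence. At ρ = 0.5 the REML-type test gives 6.8% against 7.0%, so the estimator is a minor contributor under a random intercept.
- A reader might conclude that dropout will also bias the estimates through the wrong covariance. The article states no dropout rate and the calculations assume complete data, so no such bias is shown.

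**Conclusion.** The point holds as a conditional one. The stated analysis does not secure the 0.05 used for sizing. If the usual random intercept, or intercept plus slope, is fitted, the size of the 7-degree-of-freedom interaction test lies between about 5% (no serial correlation) and about 10% (ρ about 0.9), with about 7% at ρ = 0.5. The covariance structure is the main cause. ML adds about 0.2 percentage points at N = 200 with a random intercept, but 0.7 points at N = 200 and 2.1 points at N = 76 with an unstructured covariance and a χ² reference.

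These figures rest on AR(1) deviations, complete data and an assumed visit timing; none of the correlations comes from the article. They concern the overall interaction test, not single-visit contrasts. The matter is worth correcting before analysis, but it is not proof that the planned test is invalid.

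**What to change.** Keep the fixed effects. Replace the estimation and software sentences with a REML fit that has an unstructured within-person covariance over the eight occasions (for example the R package mmrm) and Kenward-Roger or Satterthwaite degrees of freedom. Name in advance the fallback structure to be used if the model does not converge, for example heterogeneous Toeplitz, then AR(1). This ties the analysis to the unrestricted-covariance test used for sizing.

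If lme4 is kept, state the random effects and base all tests on small-sample-corrected (CR2) cluster-robust standard errors by participant. Switching from ML to REML alone is not enough, and neither is freeing the covariance with a χ² reference.

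The cost is a change of wording and one more free package. The downside is 36 covariance parameters and possible non-convergence if dropout is heavy. Enrolling 200 against a calculated 76 leaves room for a loss of up to 1 − 76/200 = 62%, so the fallback needs to be written down now.

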**Methods:**

The study is designed as a randomized controlled trial. Two hundred participants will be randomly assigned to either a mobile health intervention condition (OneUS App) or an active control condition. The intervention consists of a program to cultivate positive emotions and positive thoughts. The active control intervention will comprise a set of mental imagery exercises and daily routine recording. The primary outcome comprises optimal well-being assessed using the multidimensional PERMA-Profiler scale. The sample will include adult people from the general population, who will be assessed at 8 time points: baseline (t1), intervention (t2, t3, t4, t5, t6) post-intervention (t7) and 3-month follow-up (t8).

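### Baseline is modelled as an ordinary outcome visit and every fixed effect is tested with none named as decisive, so neither treatment test answers the directional hypothesis directly

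*Protocol article*

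**What the plan says.** The Data analysis methods section of the protocol article covers primary and secondary outcomes together. It specifies a linear mixed model, fitted by maximum likelihood with lme4, with fixed effects of condition, "time (t1, t2, t3, t4, t5, t6, t7, and t8) and Conditions x Time interaction effects". It then states: "Hypothesis tests will be conducted to assess the significance of the fixed effects".

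The Outcome measures section defines the visits as "baseline (t1), intervention (t2, t3, t4, t5, t6) post-intervention (t7), and 3-month follow-up (t8"), so t1 is measured before treatment. No baseline covariate and no equal-baseline constraint is mentioned.

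The Sample size section lists the same effects, "fixed predictors of conditions (active control and experimental), Time (t1, t2, t3, t4, t5, t6, t7, and t8), and Conditions x Time interaction effects", without saying which of them was powered. The abstract says "The primary outcome comprises optimal well-being assessed using the multidimensional PERMA-Profiler scale" and attaches no time point. The hypothesis at the end of the Introduction is directional: the app raises well-being and lowers distress.

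**The concern.** Once t1 sits among the outcome levels with a free arm difference, the two tests that involve treatment are poorly aimed at that hypothesis.

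- **Condition main effect.** It averages the arm difference over t1 to t8, including a visit at which randomisation rules out any treatment effect. Under R's default treatment coding with t1 as reference, the condition coefficient is simply the t1 difference and says nothing about treatment.
- **Condition x time.** With eight time categories and two arms this is an omnibus test on (2-1)(8-1) = 7 df. A significant result does not say when the arms differ or which arm is better.

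Reading one visit through the interaction terms gives that visit's arm difference minus the t1 arm difference. This estimates a baseline difference that randomisation already sets to zero in expectation, and it pays for that in variance. Because no effect is named as decisive, the reader also cannot tell which result would count as a positive trial. The choice can matter, since the candidate tests can differ widely in power.

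**Working it through.** **The plan's own figure.** "Using Hotelling Lawley Trace with power 0.8 and type I rate 0.05, total sample size was calculated as 76", and then "100 participants per condition will be selected to account for potential dropouts". The article states no effect size, SD or correlation for this calculation, so 76 cannot be reproduced, only back-solved. If the 7-df interaction was powered, 76 implies a squared Mahalanobis distance of 0.836. If it was a plain comparison of two means with 38 per arm, it implies d = (1.960 + 0.842) x sqrt(2/38) = 0.64. The figure fits either test, so it does not reveal which effect is decisive.

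**Precision of a single-visit contrast.** Assumptions: equal SD at all visits, 1:1 allocation ("The allocation ratio will be 1:1"), and correlation rho between t1 and the visit read. Rho is not in the documents. In units of 4 x SD^2/N:

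- change from baseline: 2(1-rho)
- baseline constrained equal, or t1 as covariate: 1-rho^2
- ratio: (1-rho^2)/[2(1-rho)] = (1+rho)/2

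| rho | change | adjusted | ratio | variance saved |
|---|---|---|---|---|
| 0.3 | 1.40 | 0.91 | 0.65 | 35% |
| 0.5 | 1.00 | 0.75 | 0.75 | 25% |
| 0.6 | 0.80 | 0.64 | 0.80 | 20% |
| 0.7 | 0.60 | 0.51 | 0.85 | 15% |
| 0.9 | 0.20 | 0.19 | 0.95 | 5% |

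For rho 0.5 to 0.7 the standard error falls by 1 - sqrt(0.75) = 13% to 1 - sqrt(0.85) = 8%. If the plain arm difference at the visit were read instead (variance 1 in these units), adjustment gives 1-rho^2, again never worse.

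**The tests the plan does name** (compound symmetry, rho 0.5 to 0.7):

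- Condition main effect: a constant post-baseline effect is diluted to 7/8 of its size. Against a baseline-adjusted mean of t2 to t8, the test loses 56% to 74% of its information.
- 7-df interaction: against the same omnibus test with baseline adjusted, the loss of noncentrality is 22% to 11% for an effect that builds up gradually, and only about 1% to 2% for an effect at t7 alone.

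**False positives if either treatment test counted as success.** Two independent tests at 0.05 give 1 - 0.95^2 = 0.0975, with an upper bound of 0.05 + 0.05 = 0.10. In 20,000 simulated null trials per setting (100 per arm, eight visits, compound symmetry), at least one test was significant in 9.7% at rho 0.5 and 9.3% at rho 0.7, with each test near 5%. These rates count rejections in both directions.

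**Power at N = 200.** Assumption: 0.3 SD at t7. This is not a protocol figure; the Introduction gives only a background pooled g of 0.17.

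| Effect shape and covariance | Condition main effect | 7-df interaction | Adjusted t7 |
|---|---|---|---|
| Gradual, half lost by t8; compound symmetry 0.6 | 0.31 | 0.61 to 0.63 | 0.75 |
| Gradual, half lost by t8; serial correlation | 0.29 | 0.35 to 0.36 | 0.72 |
| Immediate, sustained; compound symmetry 0.3 | 0.84 | not computed | 0.60 |
| Immediate, sustained; compound symmetry 0.5 | 0.69 | not computed | 0.68 |
| Immediate, sustained; compound symmetry 0.6 | 0.63 | not computed | 0.75 |
| Immediate, sustained; serial correlation | not computed | 0.85 to 0.86 | 0.72 |

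Serial correlation here means a random intercept with share 0.5 plus a component decaying by 0.7 per week. The unadjusted change at t7 has power 0.66 under compound symmetry 0.6 and 0.61 under serial correlation. The ranking of the tests depends on the shape of the effect.

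**The case against.** A condition x time model with baseline among the outcomes is a valid longitudinal analysis. It is unbiased under randomisation, and the baseline data stay in the likelihood. The primary time point, contrast coding and multiplicity are often settled in an analysis plan, which is not shown here, and the R coding remark assumes a coding that the article does not specify. Choosing t7 is itself a judgement, since the Discussion stresses lasting benefit. For an immediate, sustained effect, the averaged or omnibus test can beat a t7 contrast.

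Much of this stands. The planned tests are not invalid, and the silence on a contrast would carry little weight alone. What remains is what the article does fix: t1 is a level of time, and all fixed effects are tested. An analysis plan that constrained or adjusted for baseline would have to depart from that text. The power argument also does not rescue the t1-to-t8 main effect, because a baseline-adjusted average over post-baseline visits targets the same sustained effect without the dilution.

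Two stronger readings are tempting. A reader might infer that the plan wastes 15% to 25% of its precision. That needs rho between 0.5 and 0.7 and a change-from-baseline contrast, and the documents state neither. A reader might also infer a 10% false-positive rate. That needs a rule that either test suffices, which no section states; if only the interaction is read, the rate is 5%.

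**Conclusion.** The point holds as a weakness of aim and efficiency, not as an error that invalidates the analysis. As written, the condition effect mixes in a pre-treatment visit, the interaction is directionless, and nothing says which of them decides a directional hypothesis.

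For a single visit read as change from baseline, the avoidable variance is 1 - (1+rho)/2. That is 25% to 15% at an assumed rho of 0.5 to 0.7, and 35% to 5% over 0.3 to 0.9. The 9.75% false-positive rate is what the wording would permit under an either-test rule, not a stated property of the plan. No general claim that a t7 test has the most power is supported. The case for naming one test in advance is that the choice among them can change the conclusion.

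**What to change.** Replace the free t1 arm difference with a common t1 mean in both arms, or use t1 as a covariate with t2 to t8 as outcomes. Name one primary treatment contrast on overall PERMA, tested two-sided at 5% and reported with its 95% CI. The arm difference at t7 is one example. If a sustained effect is the main interest, a baseline-adjusted average over post-baseline visits is an alternative. Make t8, the weekly differences and the omnibus interaction secondary or supportive.

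This needs wording only, fixed before the data are seen, with no extra visits or participants. The cost is that a t7-only contrast can have less power than an averaged or omnibus test if the effect appears at once and persists, so the team should choose the contrast by the effect shape it expects.
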